**Figure 1 fig1:**
[figure not shown]
Flow chart of the planned study. EA: electroacupuncture; A: acupuncture; SA: sham acupuncture; BC: blank control; and AC: acupuncture control.

**Table 1 tab1:** The designed schedule for the data collection.

Time point	Screening period	Intervention period					Follow-up period	
	Day 0	Day1	Day 5 (Week1)	Day 10 (Week2)	Day 20 (Week4)	Once daily until discharge	Week 8 ± 3 days	Week 12 ± 3 days
Enrolment								
Informed consent	×							
Eligibility screening	×							
Randomization	×							
Allocation	×							
Interventions								
The electroacupuncture group								
The acupuncture group								
The sham acupuncture group								
The blank control group								
The acupuncture control group								
Assessments								
SFGS	×		×	×	×	×	×	×
HBGS	×		×	×	×	×	×	×
The diameter of facial nerve	×		×	×	×		×	×
Echo intensity and thickness of facial muscles	×		×	×	×		×	×
Blood flow parameters of the facial artery	×		×	×	×		×	×
Therapeutic mechanism index	×		×	×	×		×	×
Safety index	×		×	×	×			
Adverse events			×	×	×	×		
Success of blinding					×			

The treatment course will last for 20 days (4 weeks) and thereafter follow up for 8 weeks. First, the subjects will be informed of informed consent and screening. Then, they will be randomized into five different groups. The four groups related to acupuncture will be treated with acupuncture 5 times a week for a total of 4 weeks (20 days); the blank control group will receive the medicine therapy (see “Intervention” for details). The clinical data will be evaluated at baseline, days 5, 10, and 20 (weeks 1, 2, and 4), and weeks 8 and 12 of treatment. The Sunnybrook facial grading system (SFGS), the House-Brackmann facial nerve grading system (HBGS), and adverse events will be evaluated daily during treatment. During treatment, adverse events will be recorded in the Case Report Form (CRF) at any time.

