#### The blank control group

Except for the medicine therapy, no electropuncture, acupuncture, or sham acupuncture will be carried out during the whole experiment in this group.

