### Outcome measures

The outcome evaluation will be conducted at 6 time points, including the baseline, days 5, 10, and 20, and weeks 8 and 12 of treatment. In addition, SFGS and HBGS will be evaluated before each treatment to evaluate the recovery rate. Safety measures will be assessed at the baseline and day 20 of the treatment. The evaluation schedule is shown in Table 1.

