#### Primary outcome measures

The primary outcome is the effectiveness rate after the intervention period, which will be evaluated immediately at the end of treatment on the 20th day. Combined with the results of SFGS and HBGS, the efficacy evaluation criteria have been formulated according to the *Evaluation and efficacy standard of Integrated Chinese and Western Medicine for peripheral facial nerve palsy (draft)* by Yang et al. (25) as shown in Table 4. The effectiveness rate is calculated by dividing the sum of the number of cured, efficacious, and effective patients in each group by the number of patients in each group. The Sunnybrook facial grading system (SFGS) is composed of three distinct areas that generate a comprehensive score describing the overall static and dynamic state of the face. Final score = free movement points – static points – linkage points. SFGS score can range between 0 and 100, and the higher the score is, the better facial nerve function (26). The House-Brackmann facial nerve grading system (HBGS) is a scale for assessing the severity of Bell’s palsy, which can potentially classify facial nerve injury into six grades (27). Grade I indicates normal function, grade II mild dysfunction, grade ≤ IV moderate palsy, and grade ≥ V severe palsy (27). SFGS and HBGS scores will be evaluated prior to each treatment until the end of the study and during the follow-up periods of 8 and 12 weeks of treatment.

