Recovery speed: the patient’s recovery will be evaluated daily through SFGS and HBGS until the patient is assessed as “cure” according to the evaluation criteria for curative effect (Table 4). The period from baseline to this time is considered the recovery time. If the patient’s recovery time is shorter, it will be considered that the recovery speed is faster.The diameter of the facial nerve: bilateral nerve color Doppler ultrasonography will be conducted by a board-certified neurosonologist in the Department of Ultrasound of CMU1H. The diameter of the main trunk and five branches of the facial nerve on both sides of the face will be measured three times, and the average value will be taken.Echo intensity and thickness of facial muscles: the thickness and recovery strength of the frontalis muscle, the orbicularis oculi muscle, the orbicularis oris muscle, the depressor anguli oris muscle, the depressor labii inferioris, and the mentalis muscle will be measured using a diagnostic ultrasound system. The determination of maximum muscle thickness has been reported to be orthogonal to the direction of muscle fibers (19). Thus, gray analysis will be used to quantify the echo intensity of each muscle (19). The results of three independent measurements for each muscle will be averaged to minimize the differences.Blood flow parameters of facial artery: color Doppler ultrasound will be used to measure and record the systolic peak velocity (Vs), end-diastolic velocity (Vd), and resistance index (RI) of bilateral facial artery, inferior labial artery, and superior labial artery. All data will be measured three times and thereafter averaged.The serum inflammatory level: at the baseline; 5, 10, and 20 days of treatment; 8 and 12 weeks of treatment; the count of neutrophils, lymphocytes, platelets; and the levels of interleukin-6 (IL-6), interleukin-8 (IL-8), interleukin-10 (IL-10), and tumor necrosis factor-α (TNF-α) will be measured to assess the levels of immune inflammation.Safety evaluation: the various safety indicators will be measured at the baseline and the end of treatment, including blood routine (the count of neutrophils, lymphocytes, platelets, monocytes, and hemoglobin content), the liver function (alanine aminotransferase and aspartate aminotransferase), and the kidney function (blood urea nitrogen and serum creatinine).Adverse events: acupuncture can exhibit potential adverse events, such as pain, hematoma, and infection, and the participants will be clearly informed about all these adverse events before signing informed consent. We will also provide appropriate medical care for the commonly observed adverse reactions. Any adverse events will be recorded by CRF. In case of serious adverse events, treatment will be terminated, and a detailed report will be made to researchers and the ethics committee within 24 h of the occurrence. The ethics committee will make recommendations and decide whether the patient can continue the treatment. We will give them proper compensation for their medical expenses.

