### Statistical analysis

The statistical analysis of this trial will use SPSS 26.0 software. To include the data of the participants who might withdraw later from the trial, all statistical analyses were based on the intention-to-treat population of all randomly assigned patients. Missing data will be analyzed using multiple imputations using the Markov chain Monte Carlo. The continuity data will be described as mean ± standard deviation (SD) or median and interquartile spacing. The classified data will be described with the frequency and percentage (*N*, %). The assessment of the difference between groups will use repeated measure analysis of covariance (ANCOVA) and trend chi-square, and the mixed effect model will also be used to evaluate the efficacy based on adjusting possible covariates. For results that require a comparison between multiple groups, Bonferroni will be used for multiple corrections. An interim analysis will be performed when half of the participants have completed the main outcome measurement.

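### Recovery time has no value for patients who are not cured, the stated methods do not handle censoring, and the rating schedule behind it is described inconsistently

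*Protocol article*

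**What the plan says.** Recovery speed is the first secondary outcome named in the abstract and is described after the primary outcome in the outcome section. There, "the patient’s recovery will be evaluated daily through SFGS and HBGS until the patient is assessed as “cure" is reached, and then "The period from baseline to this time is considered the recovery time". Table 4 sets cure at House-Brackmann (HBGS) grade I and a Sunnybrook (SFGS) score of 90 or more. A patient who does not reach that level is given no recovery time and no end date.

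The Statistical analysis section places every analysis on the intention-to-treat population. It names repeated-measures ANCOVA, trend chi-square and a covariate-adjusted mixed model, and adds that "Missing data will be analyzed using multiple imputations using the Markov chain Monte Carlo". It assigns none of these methods to recovery time in particular.

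How often patients are rated is described in several ways:

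- Outcome measures: "SFGS and HBGS will be evaluated before each treatment to evaluate the recovery rate".
- Primary outcome measures: "SFGS and HBGS scores will be evaluated prior to each treatment until the end of the study", and also at the week 8 and week 12 follow-up.
- Notes to Table 1: the two scales "and adverse events will be evaluated daily during treatment".
- Table 1: both scales are marked in a column headed "Once daily until discharge". After day 20, the remaining marks are at weeks 8 and 12.

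For the medicine-only (blank control) arm, "no electropuncture, acupuncture, or sham acupuncture will be carried out during the whole experiment in this group".

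**The concern.** A patient rated as uncured at the last visit does not have a missing recovery time. The time is known to exceed the last visit, which makes it censored. The methods named offer two ways to handle such a patient, and neither is sound. Imputation would supply a cure date, possibly one inside a period when the patient was seen to be uncured. Leaving the patient out makes inclusion depend on the outcome, since only those who recovered are averaged, and it breaks the statement that all randomised patients are analysed.

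The uncured share is also expected to differ strongly between arms, so either shortcut affects the arms unequally. A real difference in speed could largely disappear from the reported means.

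Separately, a speed outcome depends on when patients are looked at. Rating before each treatment is clear for an arm with needling sessions and unclear for an arm with none.

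**Working it through.** **The plan's own figures.** The article gives no figure for recovery time. It does give effective rates (Sample size section): EA 98%, A 95%, AC 85%, SA 74%, BC 70%. A five-group chi-square (4 df, α = 0.05, power 0.90, likelihood-ratio effect size) with these rates gives N = 147.2, matching the stated 147. Then 147/5/0.9 = 32.7, so 33 per arm and 165 in total. The rates are therefore the ones the plan works with.

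**How many patients are uncured at day 20.** Effective covers cured, efficacious and effective (HBGS I to III), so anyone outside it is uncured:

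| Arm | Not effective | Expected of 33 |
|---|---|---|
| EA | 2% | 0.66 |
| A | 5% | 1.65 |
| AC | 15% | 4.95 |
| SA | 26% | 8.58 |
| BC | 30% | 9.90 |
| Total | | 25.74 |

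This is a lower bound, because grades II and III also count as effective without being cured. Some of these patients will be cured by week 8 or 12, but such a cure can be dated only to the gap between visits, about four weeks. The rest are censored at their last rating.

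**What a cured-only average does.** The documents give no cure rates, so these are assumed, with exponential recovery. For a fraction c cured by day T, λ = −ln(1−c)/T. The mean among the cured is 1/λ − T(1−c)/c, the median is ln 2/λ, and the restricted mean to T is c/λ. Twenty sessions at five a week with two rest days end on calendar day 26, so T = 26.

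- c = 0.40: 1/λ = 26/0.5108 = 50.90. Cured-only mean 50.90 − 39.00 = 11.90. Median 35.3. Restricted mean 0.40 × 50.90 = 20.36.
- c = 0.70: 1/λ = 26/1.2040 = 21.595. Cured-only mean 21.595 − 11.143 = 10.45. Median 15.0. Restricted mean 0.70 × 21.595 = 15.12.

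The cured-only contrast is 11.90 − 10.45 = 1.45 days. The restricted-mean contrast, which uses everyone, is 20.36 − 15.12 = 5.24 days.

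The same calculation at T = 20 over a range of cure rates:

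| Cured by day 20 | Cured-only difference (days) | Restricted-mean difference (days) | Ratio |
|---|---|---|---|
| 50% vs 30% | 0.55 | 2.40 | 0.23 |
| 60% vs 40% | 0.66 | 2.56 | 0.26 |
| 70% vs 50% | 0.81 | 2.80 | 0.29 |
| 80% vs 60% | 1.07 | 3.15 | 0.34 |
| 90% vs 70% | 1.58 | 3.81 | 0.41 |

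Dropping the uncured leaves about a quarter to two fifths of the contrast.

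**The rating schedule, side by side.** The outcome definition and the notes to Table 1 say daily. The outcome overview and the primary-outcome text tie ratings to treatments. A Table 1 column ends them at discharge. Needling runs five days a week, and Table 1 equates day 10 with week 2 and day 20 with week 4, so the trial's days look like session counts. Discharge has no clear meaning for outpatients, whom the trial recruits. Daily rating until cure also cannot continue past day 20 if the only later ratings are at weeks 8 and 12.

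**The case against.** The strongest reply is that this is a condensed article and that choosing a time-to-event method is ordinary work for a statistical analysis plan, which is not shown. No passage plans a cured-only average, and none says that cure dates will be imputed for patients seen to be uncured. That is fair as far as it goes: both distortions are consequences of the written text, not announced analyses, and the cure rates in the illustration are assumed. What remains is that the article itself fixes a definition that leaves out uncured patients, then commits every analysis to everyone randomised with a stated remedy for missing values. Those statements do not fit together.

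A reader might also infer that the needled arms are rated at every session and the medicine-only arm only at the scheduled visits, so that cure is detected later without needling and the comparison favours acupuncture. The documents do not support this. The outcome definition, the notes to Table 1 and Table 1 itself describe daily rating without restricting it to any arm, and the blank control section says nothing about ratings. If the medicine-only arm were seen only on days 5, 10 and 20 and another arm daily, identical recovery would look 3.0 to 3.2 days slower there (exponential recovery, 30% to 90% cured by day 20). That schedule is hypothetical, and it would affect only comparisons with that arm. The four needled arms share a session schedule, so the sham comparison would not be affected. What stands is the inconsistent wording.

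**Conclusion.** The point holds for the definition and for its mismatch with the stated methods. At least about 26 of 165 patients are expected to be uncured at day 20, ranging from 2% to 30% by arm. That rests only on the article's planning rates and is a lower bound. The number never cured by week 12 cannot be derived from the documents. The attenuation to about a quarter to two fifths rests on assumed exponential recovery and assumed cure rates, and it applies only if uncured patients are dropped.

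The rating schedule needs reconciling, but the text does not establish a difference between arms or a bias in favour of acupuncture. The outcome is secondary and the sample size does not depend on it. The point should be settled before analysis, but it does not threaten the primary result.

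**What to change.** Define the outcome as time to first rating of cure in all randomised patients and analyse it as time-to-event data. Censor uncured patients at their last assessment and state that cure times are not imputed. Treat a cure first seen at week 8 or 12 as interval-censored since the previous rating. Present Kaplan-Meier or Turnbull curves, and compare arms with a Cox or interval-censored model adjusted for baseline HBGS grade.

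Reconcile the passages on rating frequency into one schedule common to all five arms, saying what it means for medicine-only patients and for outpatients. If the schedules do differ by arm in practice, date cure from the scheduled visits that all arms share.

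The cost is a change of wording and a little more analysis work. Dating cure from common visits only would make the timing coarser, so that step should be kept for the case where schedules really differ.

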### Data collection

The CRF will be completed by the clinical investigator. Clinical investigators will have to ensure accuracy, completion, and timely loading of data into CRF while preserving the original records. The completed CRF and other scales will be reviewed by the clinical supervisor and transferred to the data manager. To reduce shedding and increase study compliance, the investigator and data collector will remind the subjects about this procedure 1 day before the scheduled visit date.

### Data management

There will be two data administrators entering and proofreading the data to ensure accuracy. If any problem is detected with the data, the data supervisor will ask the researcher for clarification. After the study, the clinical researchers, data managers, and statistical analysts will carefully review the established database. After a blind audit and confirmation of the correctness of the established database, principal researchers and statistical analysts will lock the data. The locked data files will remain unchanged. The data will only be used for this specific research project.

### Confidentiality

All information collected during the study will be kept confidential and held by the investigator. The various researchers, members of the ethics committee, and relevant management departments have the right to review the information records of the participants to the extent permitted by the law. The personal information of the participants will not be independently disclosed in any research report or publications related to the project.

### Patients and public involvement

Patients and the public will not participate in the analysis and evaluation of the results of this study. The results will be disseminated through publication in peer-reviewed journals.

### Statistical analysis

The statistical analysis of this trial will use SPSS 26.0 software. To include the data of the participants who might withdraw later from the trial, all statistical analyses were based on the intention-to-treat population of all randomly assigned patients. Missing data will be analyzed using multiple imputations using the Markov chain Monte Carlo. The continuity data will be described as mean ± standard deviation (SD) or median and interquartile spacing. The classified data will be described with the frequency and percentage (*N*, %). The assessment of the difference between groups will use repeated measure analysis of covariance (ANCOVA) and trend chi-square, and the mixed effect model will also be used to evaluate the efficacy based on adjusting possible covariates. For results that require a comparison between multiple groups, Bonferroni will be used for multiple corrections. An interim analysis will be performed when half of the participants have completed the main outcome measurement.

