**Methods and analysis:**

In this randomized, controlled trial, 165 Bell’s palsy patients with unilateral onset within 3 days will be recruited and randomly assigned to either the electroacupuncture group (*n* = 33), the acupuncture group (*n* = 33), the sham acupuncture group (*n* = 33), the blank control group (*n* = 33), or the acupuncture control group (*n* = 33) in a 1:1:1:1:1 ratio. The participants will receive 4 weeks of treatment and 8 weeks of follow-up. The five groups of participants will receive the following treatments: A: Electroacupuncture + Medication (prednisone acetate tablets, mecobalamin tablets, and vitamin B1 tablets); B: Acupuncture + Medication; C: Sham Acupuncture + Medication; D: Medication only; and E: Acupuncture only. The primary outcome will be the effectiveness rate of different acupuncture modalities in improving facial nerve function after the intervention period. The secondary outcomes will be the recovery speed, the diameter of the facial nerve, the echo intensity and thickness of facial muscles, blood flow parameters of the facial artery, the serum inflammatory level, safety evaluation, and adverse events. Preliminary exploration of its mechanism of action occurs through inflammation and immune response. The difference between groups will be assessed using repeated measure analysis of covariance (ANCOVA) and trend chi-square.

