### Sample size

The calculation of the sample size is based on the effective rate of acupuncture in the treatment of patients with Bell’s palsy in the acute stage. According to the previous studies (22, 23) and pre-experimental analysis of the research group, it is estimated that the effective rate of the EA group is 98%, the A group is 95%, the AC group is 85%, the SA group is 74%, and the BC group is 70%. We used PASS 15 software to calculate and set α = 0.05 and β = 0.1, and the results showed that the total sample size was at least 147 cases. It was observed that based on the ratio of the sample size of 1:1:1:1:1 in each group and considering the loss of follow-up rate of 10%, an optimal sample size of 33 participants should be recruited in each group. Therefore, a total of 165 participants should be recruited for this RCT.

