### Interventions

The interventions will be combined with the guidelines (3) published by the American Academy of Neurology (AAN) and the American Academy of Otolaryngology-Head and Neck Surgery Foundation (AAO-HNSF) in 2013 and the preliminary experiments of this study (2). Acupuncture will be performed by three different experienced acupuncturists in accordance with STRICTA (19). The subjects in each group, except the blank control group, will receive either acupuncture, electroacupuncture, or sham acupuncture treatment 5 times per week for 4 weeks. Except for the acupuncture control group, patients in each group will receive the following medications. Prednisone acetate tablets will be administered orally at 30 mg per day for 5 days, then it will be reduced by 5 mg per day until discontinued for 10 days (Sinopharm, Rongsheng Pharmaceutical Co. LTD., Jiaozuo, China); Mecobalamin tablets of 0.5 mg will be orally administered, 3 times a day (Eisai (China) Pharmaceutical Co., LTD., Jiaozuo, China); and Vitamin B1 tablets of 10 mg will be administered orally 3 times a day (Fuzhou Haiwang Fuyao Pharmaceutical Co., LTD., Fuzhou, China). During the study, subjects will not be allowed to use traditional Chinese medicine treatment methods other than those prescribed medications to treat the disease (e.g., traditional Chinese medicine preparations, tuina therapy, etc.). The participants can withdraw from the trial for any reason and at any point in time. Researchers can remove participants from the trial with any of the following conditions: (1) the legal representative of the patient requested to withdraw from the study, (2) serious adverse events, and (3) death.

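### The Bonferroni and all-randomised rules are not limited to efficacy, so as written they also cover harm comparisons, where Bonferroni costs much of the power at 33 per arm

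*Protocol article*

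**What the plan says.** The Statistical analysis section sets one group of rules for the whole trial.

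- Population: "all statistical analyses were based on the intention-to-treat population of all randomly assigned patients".
- Multiplicity: "For results that require a comparison between multiple groups, Bonferroni will be used for multiple corrections". The number of comparisons is not given.
- Missing data: "Missing data will be analyzed using multiple imputations using the Markov chain Monte Carlo".
- Only one sentence is limited to efficacy, the one on modelling: "the mixed effect model will also be used to evaluate the efficacy based on adjusting possible covariates".

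Safety is among the outcomes to which these rules apply. The Abstract ends its list of secondary outcomes with "the serum inflammatory level, safety evaluation, and adverse events", and the Outcome measures section describes both the laboratory safety panel and adverse-event recording. The Interventions section also states "Researchers can remove participants from the trial with any of the following conditions" and includes serious adverse events among those conditions.

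**The concern.** Bonferroni limits false positive claims. For efficacy that protects the reader from unfounded claims of benefit. For harm the costly error is the opposite one, a real difference passed over, and a stricter threshold makes that error more likely. An all-randomised denominator likewise lowers a harm rate when it counts patients who were never exposed.

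This matters here because the Introduction presents the trial as a response to the worry that needling in the acute stage may aggravate nerve edema, and the Discussion treats acute-stage use, of electroacupuncture above all, as unsettled. With five arms of 33, a sizeable imbalance in adverse events could be reported as not significant merely because the efficacy correction was carried over to it.

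**Working it through.** **Inputs.** From the Sample size section: 33 patients per arm and "set α = 0.05 and β = 0.1". The 33 follows from the plan's own figures: 147 / 0.9 = 163.3, so 164; 164 / 5 = 32.8, so 33 per arm and 165 in total. A likelihood-ratio five-group chi-square on the assumed effective rates gives N = 147.2, matching the stated 147. The plan gives no adverse-event rates, so all event rates below are assumptions, shown over a range.

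**Bonferroni levels.** Four comparisons (for example each arm against one reference): 0.05 / 4 = 0.0125. All pairs of five arms: 5 × 4 / 2 = 10, so 0.05 / 10 = 0.005.

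**Power.** Exact enumeration over all tables with n = 33 per arm: power = Σ Bin(a; 33, p1) × Bin(b; 33, p2), summed over the pairs (a, b) whose two-sided p-value is at or below the level. Chi-square uses the pooled variance without continuity correction.

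| Event rates | Chi-square at 0.05 / 0.0125 / 0.005 | Fisher at 0.05 / 0.0125 / 0.005 |
|---|---|---|
| 15% v 3% | 43.6 / 18.2 / 4.8% | 18.8 / 8.8 / 4.3% |
| 15% v 0% | 75.0 / 37.4 / 11.1% | 37.4 / 21.7 / 11.1% |
| 25% v 3% | 81.5 / 60.6 / 35.5% | 63.9 / 42.4 / 30.0% |
| 30% v 5% | 81.9 / 63.5 / 42.5% | 70.1 / 47.9 / 33.6% |
| 40% v 5% | 96.3 / 88.9 / 77.5% | 92.8 / 81.4 / 68.7% |

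Against 0 of 33, the fewest events in the other arm that reach significance are 4, 6 and 8 by chi-square and 6, 7 and 8 by Fisher, at the three levels in turn.

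**All-randomised denominator.** If a fraction f is never treated and has no treatment-related events, each rate is multiplied by (1 − f). For 25% v 5% the 20-point difference becomes 20 × 0.97 = 19.4 points at f = 3% and 20 × 0.90 = 18 points at f = 10%. By the normal approximation, power at 0.05 with f = 10% is 57.4% in all randomised patients against 58.2% in treated patients. With f = 0 there is no effect.

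**Imputation.** A simulated day-20 laboratory value with a true between-arm difference of 0.50 SD compared regression imputation (standing in for the mean of multiple imputations) with complete cases. Missingness was either 10% at random, or 40% when a driving value exceeded 1 SD and 3% otherwise.

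| Missingness | Full data | Complete cases | Imputed, day 10 used | Imputed, baseline only |
|---|---|---|---|---|
| Completely at random | 0.50 | 0.50 | 0.50 | 0.50 |
| Driven by the day-10 value | 0.50 | 0.46 | 0.50 | 0.48 |
| Driven by the unseen day-20 value | 0.49 | 0.44 | 0.47 | 0.46 |

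Imputation understated harm when missingness depended on the unseen value, or when the imputation model lacked the value that drove it. Complete cases did worse in both settings.

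**The case against.** **The article is condensed.** A separate safety set and safety-specific methods may be in an analysis plan that is not shown, and their absence is no finding. That stands. The finding is the stated scope: a later document that defined a safety set would conflict with a sentence covering every analysis.

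**Bonferroni is conditional.** No section says that adverse events or laboratory safety will be tested between arms, and frequencies and percentages will be displayed whatever the p-value. A reader might infer that the protocol commits to testing harms at 0.005. It does not. The application to safety follows from unrestricted wording, and 0.005 is the worst case. The loss at 0.0125 is still large.

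**Small counts flatter the uncorrected chi-square.** This is correct, and most visible at 15% v 0%, where Fisher's power at 0.05 is 37.4% and not 75.0%. Detecting uncommon harm is weak at this size even uncorrected. Fisher's test still loses power at each rate tried.

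**The all-randomised sentence has a good purpose.** It keeps patients who withdraw in the analysis, and their harm data with them. Allocation is sealed until the first treatment, so few should be randomised and untreated. A reader might take the planned 10% loss to follow-up as a guide to how many never start. It is a different quantity, and the documents give no figure for that.

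**Imputation.** A reader might infer that all three rules push toward no harm, with harmed patients who leave being replaced by healthy values. The documents and the check do not support this. Multiple imputation has no built-in direction, it was no more attenuated than complete cases, and adverse events are recorded as they occur, so one that leads to withdrawal is already observed.

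**Oversight is separate.** The safety board reviews the trial every six months and can see allocation. That protects participants during the trial but does not govern the reported comparison.

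**Conclusion.** The concern holds as a fault of scope in a stated rule. As worded, Bonferroni reaches any between-arm harm comparison and the all-randomised set reaches every harm rate.

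The Bonferroni part is material: at 25% v 3%, it removes about 21 to 46 points of chi-square power (81.5 − 60.6 = 20.9; 81.5 − 35.5 = 46.0) or about 22 to 34 points of Fisher power (63.9 − 42.4 = 21.5; 63.9 − 30.0 = 33.9), for four and ten comparisons. These sizes rest on assumed event rates and on safety actually being tested between arms.

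The denominator part has a clear direction but is probably small. Imputation is a conditional concern only: it matters if day-20 laboratory values are missing because of toxicity that no recorded value captures. Removal for serious adverse events makes that possible but does not show that it will happen.

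**What to change.** In the Statistical analysis section, limit the Bonferroni and all-randomised rules to efficacy, and add text such as:

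*Adverse events and laboratory safety are analysed in patients who received at least one session or dose, by treatment received. Rates and between-arm differences are given with unadjusted 95% confidence intervals. Observed laboratory values, including the last on-treatment value of patients who stop early, are shown beside any imputed analysis.*

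Show both laboratory analyses, since complete cases alone were the more attenuated in the check and use of the last on-treatment value was not tested there. Also reconcile the laboratory safety schedule, because it decides how much on-treatment data exists: Table 1 marks days 5 and 10 as well, while the Outcome measures text names only baseline and the end of treatment.

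The cost is wording and the approvals that the protocol requires for any modification. No patients, visits or procedures are added. Without a correction more safety differences will arise by chance, and the report should present them as signals and not as claims.
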